## Methods

### Design

The trial will take place in government-funded secondary schools in the Western Sydney region of Australia, one of the fastest growing areas in the nation. This region has a large proportion of youth who come from low socio-economic status (SES) and immigrant backgrounds [43, 44], meaning they are at greater risk of physical inactivity compared with the Australian average [45].

This will be a two-arm, cluster randomized controlled trial with allocation at the school level (1:1 ratio to intervention and control conditions). See CONSORT flow diagram (Fig. 2). School years in Australia run from the end of January to the middle of December, with a summer break from mid-December to late January. Assessments will be completed at baseline of the first year (Term 1, February-April) and post-intervention (Term 4, September-December 2014: 7–8 months after baseline), which is the primary endpoint for this trial. A maintenance phase assessment will be conducted 14–15 months after baseline (Term 2, May–July).

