### Sample size

Sample size calculations were based on estimated effect sizes for the primary outcome. A recent meta-analysis [3], indicated that lesson planning and delivery interventions have a pooled effect of *d* = 0.60 on MVPA during PE lessons. To ensure 80 % power to detect an effect of this size would require 90 participants in a non-clustered trial (two-tailed probability level of 0.05). We considered the clustered nature of the data, including both school and class levels [46]. However, results from recent studies of MVPA in PE lessons indicated that clustering at the school level was negligible after accounting from clustering at the class level [22, 33]. As a result, we adjusted our sample size calculations for clustering using the formula 1 + (*m*-1)ρ, where *m* is the number of students per class and ρ is the intra-class correlation (ICC) [46].

Our recent study in Sydney-area schools indicated a class-level ICC of 0.62 [22], which was similar to Aelterman et al. [33] who reported a class-level ICC of 0.63. With an estimated class size of 22 participating students, an adjustment of 14.23 was required: 1 + (22–1)*0.63 = 14.23. Multiplying by the 90 participants required in non-clustered trial, we estimated that 1280 students would need to participate to achieve 80 % power. We estimate that 14 schools, with a mean of 4.5 classes of Year 8 students per school can be recruited and, therefore, aim to recruit 1386 students (14 schools × 4.5 classes per school × 22 students per class). Potential loss to follow up of up to 30 % of participants (*n* = 384; a very conservative estimate) will not substantially impact on the statistical power of the study. This resilience to loss of power exists because this study will use generalized mixed models, enabling the inclusion of all participants (included at baseline) in the analyses. In non-clustered longitudinal clinical trials, this analytic approach has been shown to yield similar point estimates and smaller decreases in statistical power than multiple imputations [47, 48].

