### Recruitment and randomization

Principals and Head Teachers of PE from all secondary schools that meet our eligibility criteria will be invited to express their interest in participating in this study. From the schools that indicate an interest in the study, we will attempt to purposively select schools in order to ensure that the sample is representative of the region’s population, in terms of school size and gender composition (i.e., single sex or co-educational). Schools that agree to participate will be match paired according to SES of the postcode in which the school is located (according to the Index of Relative Socio-Economic Disadvantage:), school size (Year 8 enrolment), gender composition of PE classes (i.e., single sex vs co-ed) and the duration of PE lessons. Using a computer-based randomization plan generator, the 14 schools will be randomized to the control or intervention condition from within each pair following baseline assessments. A researcher not associated with recruitment or data collection, and who will be blind to school identity, will carry out randomization procedures.

All PE teachers in schools that enter the trial will be invited to an information session during which study procedures will be outlined and questions answered. The research team will present study information and provide an information letter and consent form to all Year 8 students from classes whose teacher agrees to participate.

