### Statistical analysis

Between-arm differences in changes on the primary and secondary outcomes will be analyzed using generalized linear mixed models according to intention-to-treat and per-protocol principles. Specifically, intention to treat analyses will involve analysis of outcomes collected from all students who completed baseline assessment, regardless of whether or not they complete post-intervention or maintenance phase assessments. Between-arm differences in changes on the primary and secondary outcomes will be assessed by including an indicator variable for group allocation (arm), a variable representing time (baseline, post-intervention, and/or maintenance) and their interaction.

For the primary outcome (MVPA during lessons), student data will be gathered from between one and three lessons per student at each of the time points (baseline, post-intervention and maintenance). The repeated measure will be modeled as a random intercept effect. Lesson will also be modeled as a random intercept effect. Analyses will also be adjusted for class and teacher clustering-each teacher will be given a case ID. In instances where teachers ‘team-taught’ (i.e., two teachers within a single lesson), we will create a new case ID that is unique to that combination of teachers. In some instances students will be taught by different teachers within a time point (i.e., from lesson to lesson) or across time points (e.g., from baseline to post-intervention). We will account for this data structure by specifying cross-classified random effects models. Possible school-level residual clustering will be explored and included in the models, if appropriate. In sum, we will include four random intercept effects: (i) lesson; (ii) student; (iii) teacher; and (iv) class. We will consider a fifth random intercept effect for school, if preliminary analyses suggest clustering of MVPA during lessons at the school level.

We will also control for a number of variables that could influence students’ MVPA during lessons. These include temperature at the start time of the lesson, the type of activity included in the lesson and the timing of accelerometer fitting for the lesson (the student arrived at lesson wearing an accelerometer or was fitted at started of lesson).

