Generalized linear mixed models will be also used to examine mediation hypotheses. Mediating effects will be estimated using a cluster-bootstrapped based product-of-coefficients test that is appropriate for cluster randomized controlled trials [75].

Potential moderators of the intervention effects will also be explored. Potential moderators will include gender and ethnic background (categorical variables), as well as socio-economic status and baseline levels of physical activity and psychosocial variables (e.g., motivation and needs satisfaction) which will be treated as continuous variables. Moderator effects will be explored using the same generalized mixed modeling approach by including appropriate interaction terms in the regression models. The trial is powered to detect main effects, not interactions; thus, we will employ a less stringent significance level to explore potential moderators. Interaction terms that are significant at *p* < 0.1 will be explored by testing differences in intervention effects across sub-groups stratified according to the moderator variable [76].

Per protocol analyses will investigate the influence of teachers’ adoption of the intervention, as indicated by the proportion of intervention components completed by each teacher (e.g., workshops attended and online tasks completed), on student outcomes (e.g., MVPA during PE lessons). Analyses will also examine the effect of teachers’ implementation of the intervention, as indicated by increases in their use of AMPED teaching strategies from baseline to post-intervention (observed in video recordings of their lessons), on student outcomes.

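### The gender pairing factor has only two levels, so a boys' school and a girls' school tie on it and could be paired, which would split that pair by sex between the arms

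*Protocol article*

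**What the plan says.** All of the design text is in the protocol article, Recruitment and randomization. Schools are to be chosen purposively from those that express interest, so that the sample reflects the region "in terms of school size and gender composition (i.e., single sex or co-educational"). Single-sex schools are therefore expected as possible members of the sample, but no number is given.

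On pairing: "Schools that agree to participate will be match paired according to SES of the postcode in which the school is located", on Year 8 enrolment, and on "gender composition of PE classes (i.e., single sex vs co-ed) and the duration of PE lessons". Then "the 14 schools will be randomized to the control or intervention condition from within each pair following baseline assessments". The Design section confirms "allocation at the school level (1:1 ratio to intervention and control conditions").

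In Statistical analysis, the effect is the arm-by-time interaction in a mixed model, that is, a between-arm difference in change. On adjustment for the primary outcome the text says: "These include temperature at the start time of the lesson, the type of activity included in the lesson", followed by the timing of accelerometer fitting. Student sex is not named. It enters later, for exploration: "Potential moderators will include gender and ethnic background (categorical variables").

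**The concern.** Pairing on gender composition should make the two schools of a pair alike in that respect. With the levels single sex and co-ed, it makes them alike in class format but not in which sex is taught. If the 14 schools included one boys' school, one girls' school and no other school with single-sex PE classes, strict use of this factor would bring those two together. In that pair, sex and arm would coincide completely.

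The protocol also uses two different constructs. Selection refers to the school's gender composition, while pairing refers to that of PE classes. A co-educational school that teaches PE in single-sex classes counts as single sex for pairing, although it enrols both sexes. It therefore ties with a boys-only or girls-only school as well.

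With 7 pairs there is little room for an imbalance to average out. What is at stake is precision of the primary contrast and, in an affected pair, a gender-moderator comparison that cannot separate sex from school.

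**Working it through.** **Inputs from the protocol.** 14 schools, hence 7 pairs; 1:1 allocation within pairs; d = 0.60; 90 students unclustered; class size 22; ICC 0.63; target 1386 students.

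**The plan's own figure.** A two-sample t-test with d = 0.60, two-sided alpha 0.05 and 80% power needs 44.6, so 45 per arm, or 90 in total. The design effect is 1 + (22 − 1) × 0.63 = 14.23, and 90 × 14.23 = 1280.7, against the stated 1280. It reproduces. The point made here does not change it.

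**Planned precision.** Effective sample size = 1386 / 14.23 = 97.4. Standard error of the arm difference = 2 / √97.4 = 0.203 SD.

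**Assumptions not in the documents.** The 7 pairs are of equal size. All other pairs have 50% boys in both arms. The number of boys'/girls' pairs is k = 1 or 2. The sex difference in change, δ, is 0.1 to 0.3 SD, the same in both arms.

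**Sex imbalance between arms.** The difference in the share of boys is k/7 when all k pairs fall the same way.
- k = 1: 1/7 = 14.3 points, so 57.1% versus 42.9%.
- k = 2: 2/7 = 28.6 points, so 64.3% versus 35.7%, with probability 0.5. Otherwise the two pairs offset each other and the difference is 0.
- If instead a boys-only school is paired with a co-educational school that has single-sex classes (half boys), the difference is (1.0 − 0.5)/7 = 7.1 points.

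**Shift in the arm contrast.** Largest shift = kδ/7.

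| k | δ = 0.1 SD | δ = 0.3 SD | Share of d = 0.60 |
|---|---|---|---|
| 1 | 0.014 SD | 0.043 SD | 2% to 7% |
| 2, same direction | 0.029 SD | 0.086 SD | 5% to 14% |

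**Loss of precision.** The sign is random, so the shift has mean zero and standard deviation δ√k/7. The standard error is multiplied by √[1 + (δ√k / (7 × 0.203))²].
- k = 1: 0.2% for δ = 0.1 and 2.2% for δ = 0.3.
- k = 2: 0.5% for δ = 0.1 and 4.4% for δ = 0.3.

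**If the sex difference lies in response to the intervention.** Only the intervention arm is affected. Its share of boys moves from 1/2 to 1/2 + k/14, so the shift is kδ/14, half of the figures in the table.

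**The case against.** The strongest reply is that the harmful pair is possible but nowhere planned. It needs a boys-only and a girls-only school, both interested, both selected, and close to each other on SES, enrolment and lesson duration as well. Gender is one of four factors, so a tie on it does not make two schools a perfect match. Two schools coded single sex may also both be co-educational with single-sex classes, and then no imbalance follows. All of this stands, and it makes the point conditional.

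A second reply is that the words in brackets are a short gloss in a condensed article, and that the covariate list is open-ended, so an analysis plan may add sex. The part on covariates stands: not naming sex is no fault in itself. The part on pairing does not. The two levels are what the protocol states, and an analysis plan can adjust for a pairing but cannot undo it.

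Two stronger readings are tempting. A reader might infer that the primary result would be systematically biased. The documents do not support this: arm is assigned at random within the pair, so a sex difference in trend adds variance with a random sign. A reader might also take a sex gap in the level of MVPA, say 0.5 SD, and obtain a shift of 0.07 to 0.14 SD and a standard error 6% to 12% larger. Those figures apply to a comparison at a single wave. The protocol plans a difference in change for primary and secondary outcomes, in which a stable gap largely cancels, so they should not be used.

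**Conclusion.** The point holds as a conditional weakness of the pairing rule. As written, the gender factor does not separate boys' from girls' schools, the sample may contain both, and no named covariate adjusts for sex. If one such pair is formed, one sex falls wholly in each arm of that pair, and the arms overall differ by about 57% versus 43% boys. The consequence is modest: a chance shift of 0.014 to 0.043 SD with one pair, at most 0.086 SD with two, or a standard error larger by roughly 0.2% to 4%. These sizes rest on the assumed sex difference in change of 0.1 to 0.3 SD, which the documents do not give, and on equal pairs. The number of single-sex schools, on which everything depends, is not stated. The point deserves action because it is almost free to remove, not because the trial's conclusion is threatened.

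**What to change.** In Recruitment and randomization, before schools are paired, code the gender factor so that boys-only and girls-only schools are different levels, and state that they will not be paired with each other where the other factors allow. It is also worth saying how a co-educational school with single-sex PE classes is coded. In Statistical analysis, add student sex and its interaction with time to the primary model. The planned gender-moderator analysis needs these terms in any case, and they protect the contrast if a mixed pair cannot be avoided.

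The cost is a sentence in each section and slightly less freedom in matching on SES, school size and lesson duration among 14 schools. Requiring even numbers of boys-only and girls-only schools is not advisable, because it may conflict with the protocol's aim of a sample that represents the region.

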### Intervention

#### Overview

An overview of the intervention can be found in Table 1. During the main portion of the intervention (six months: Terms 2 and 3 of 2014), teachers will participate in two days of face-to-face workshops at a local university and complete two implementation tasks at their school. These implementation tasks will involve video-based self-reflection via the project’s Web 2.0 platform and an individualized feedback meeting with a project mentor. Each intervention school will also complete two group peer-mentoring sessions at their school (one per term) in which they will discuss implementation with members of their school PE staff.

In the booster period (Term 1 of 2015), teachers will complete a half-day face-to-face workshop at their school, plus one implementation task and a group mentoring session at their school. Throughout the entire intervention period (main intervention plus booster period), teachers will have access to online resources, including videos of good/poor practice, sample lesson plans and a discussion forum. The NSW Board of Studies, Teaching and Educational Standards has accredited this training.

#### Main intervention

##### Face-to face professional development workshops for teachers

During the main intervention period (Terms 2 and 3, Year 1), training will involve two days of face-to-face workshops, including presentations by members of the research team (CL and DL), videos of best/poor practice examples viewed on the project website, video-based self-reflection via the project website, group discussion, opportunities for teachers to practice implementing taught principles in simulated scenarios, and action planning (i.e., goal-setting) via the project website. All workshops will take place at Western Sydney University, where key facilities include a large classroom and a gymnasium. A complete listing of workshop components can be viewed in Additional file 1: Appendix A.

Workshop training will have two broad aims: (i) to teach teachers motivational strategies that can be implemented in their PE lessons; and (ii) to help teachers plan and deliver lessons that maximize opportunities for MVPA.

Lesson planning and delivery strategies are based on interventions previously employed in large-scale trials mostly in the United States [10, 11, 49]. Briefly, these strategies are designed to create teacher awareness of PA and sedentary behavior levels in their lessons, minimize management and instruction time, and maximize opportunities for PA [10]. Motivational strategies are based on SDT tenets. The goal of this portion of the training is to teach PE teachers how to support their students’ basic psychological needs during lessons, thus promoting autonomous motivation towards PE and leisure-time PA. Details of all AMPED strategies can be viewed in Table 2.

**Table 1 Tab1:** Overview of intervention components

Phase	Component	Timing
Main Intervention (Year 1)	Face-to-Face Workshop 1 (1 day)	Start of Term 2, May
	Technology-assisted Implementation Task 1	Term 2, May–June
	Group Mentoring Session	End of Term 2, June
	Face-to-Face Workshop 2 (1 day)	Start of Term 3, July
	Technology-assisted Implementation Task 2	Term 3, July–September
	Group Mentoring Session	End of Term 3, September
Booster Intervention (Year 2)	Face-to-Face Workshop 3 – Booster (1/2 day)	Start of Term 1, February
	Technology-assisted Implementation Task 3	Term 1, February–March
	Group Mentoring Session	End of Term 1, March

**Table 2 Tab2:** AMPED Intervention principles and teaching strategies

AMPED Principles	AMPED Teaching strategies
Maximising Movement and Skill Development	1. Include an active warm-up with dynamic stretching.
	2. Provide lots of equipment.
	3. Employ circuits and rotations.
	4. Use grids effectively.
	5. Implement small sided games.
	6. Organise non-elimination games.
	7. Modify games to maximize activity and skill development.
	8. Integrate fitness into activities.
	9. Choose activities that maximize MVPA.
Reducing Transition Time	1. Manage the change room effectively.
	2. Take the roll while students are active.
	3. Early activity set-up.
	4. Distribute equipment quickly.
	5. Decrease talk/instructions.
	6. Form groups efficiently.
	7. Manage water breaks efficiently.
Building Competence	1. Provide overview of lesson/unit.
	2. Make behavioural expectations clear.
	3. Use questioning.
	4. Provide effective positive feedback.
	5. Provide effective corrective feedback.
	6. Match task to ability level.
	7. Limit peer comparison.
	8. Promote self-comparison.
Supporting Students (including support for students’ autonomy and relatedness needs)	1. Emphasise fun and variety.
	2. Circulate around the class.
	3. Provide students with opportunities to make choices.
	4. Provide a rationale and emphasise relevance.
	5. Minimise controlling language and behavior.
	6. Take the students’ perspective.

Definitions for each principle and strategy can be found in Additional file 1.

Importantly, many aspects of the face-to-face workshop will be delivered using web-based resources. For example, best/poor practice videos will be accessed through the project website during face-to-face workshops. Teachers will also conduct their first self-reflection task during the workshop by accessing videos of their lessons that will be uploaded onto the project website. Teacher self-reflection will involve a rating of their implementation of each AMPED strategy (1 to 5 stars) and free-text response explaining why they provided this rating. See an example in Fig. 3. Additional file 1: Appendix B provides details of all ratings and descriptions. Thus, for much of the workshop, teachers will work independently on the web platform, but project staff will be available to provide assistance at any stage.

**Fig. 3 Fig3:**
[figure not shown]
Screen shot of a self-reflection exercise on the AMPED website.

All teachers in the intervention condition will be provided with a touchscreen tablet computer (iPad) to use during the workshops and implementation in their schools. Using this technology will allow us to blend learning during the face-to-face workshops with implementation tasks completed in schools. It is important to provide this equipment to teachers as pilot work in local schools showed that many computers in NSW Department of Education schools operate outdated versions of web browsers that do not support the project’s website. Many teachers suggested that updating computer software would be a significant barrier to implementation, as it required a school network administrator to complete the process.

##### Technology-assisted implementation in schools

Teachers in the intervention condition will have access to the project’s interactive website. The site guides teachers through a series of three implementation tasks, with one task to be completed after each face-to-face workshop (two during main intervention, one during booster intervention).

The first step in each implementation task will require teachers to set an ‘action plan’ (i.e., goals) for implementation of AMPED strategies taught during the face-to-face training workshop into their lessons during the month following the workshop. The second task will require teachers to reflect on their implementation of AMPED strategies, using video clips of their teaching during the month following the workshop. Specifically, project staff will film a scheduled lesson occuring after the workshop, which will then be analyzed using a coding system designed to identify events that take place during lessons and are relevant to principles taught during the face-to-face workshop. For example, each time a teacher provides students with feedback during a lesson, this event will be ‘tagged’ and a short video clip containing all instances of teacher feedback will be uploaded to the website. Teachers can then reflect on the extent to which this feedback aligns with strategies designed to support students’ psychological needs (e.g., Fig. 3).

The third and final step in the implementation task will involve a mentoring conversation at each teacher’s school. Following each self-reflection task, teachers will meet with one of three mentors who are part of the project team. A mentor will review each teacher’s video clips and then facilitate a feedback conversation with the teacher. This conversation will be the final step in the first implementation task. Mentors will then help teachers to set a new action plan for implementation over the remainder of the term.

Project mentors will have at least three years of experience teaching PE and will complete two days of training designed to ensure in-depth understanding of AMPED intervention principles. This training will involve reading and discussing SDT-related research papers, learning about the mentors’ role and participation in the intervention, and practice using the video coding system and website for viewing mentees’ videos. The peer mentors will also practice their mentoring skills in mock mentoring sessions, reflect on their own mentoring practice and provide feedback on the other peer mentors’ performance.

Teachers will complete the implementation task three times-once following each workshop. They will also participate in three group mentoring conversations at their school-once per term during the two main intervention terms and once during the booster period. These group mentoring sessions will take place at each school and involve PE staff members from that school. The purpose of these sessions is to encourage staff to reflect on their implementation of AMPED strategies and devise methods to support each other’s implementation in the future. A project mentor will lead the first group mentoring session. A member of each school’s PE staff will lead the second mentoring session, with the project mentor observing and providing the staff member with private feedback following the session. The staff member will lead the third and final group mentoring session on his/her own during the booster period.

In addition to facilitating teachers’ implementation tasks, the project website will provide teachers with resources designed to facilitate successful implementation of principles from the face-to-face workshops. The site utilizes a Web 2.0 platform that allows for dynamic interaction between the teachers and the research team. For example, teachers will be able to rate and comment on each of the resources that the research team posts on the site. This teacher feedback will automatically update the list of top rated resources on the site. Resources will also be ‘pushed’ to teachers when they create each action plan. Specifically, each resource will be linked via a database to relevant AMPED strategies. Thus, when a teacher includes an AMPED strategy as part of an action plan, an email will be sent to the teacher with links to relevant resources that will aid implementation.

The web platform also includes a community of practice discussion forum where teachers can share experiences from their attempts to implement specific strategies from the intervention in their own PE lessons. The project manager, with input as required from the project mentors and lead investigators, will moderate the discussion and provide ongoing advice to help teachers overcome barriers to implementation.

Teachers will also be able to download an AMPED mobile application (‘app’) that provides reminders to implement their chosen strategies at an interval of their choosing (range = once per day to once every eight weeks). The app will also prompt teachers to conduct brief self-reflections on their implementation of AMPED strategies, with the same interval range as the reminder function. See Fig. 4 for screenshots from the app.

